## Abstract

**Background:**

Tuberculosis preventive treatment (TPT) is essential for tuberculosis elimination; however, evidence on its safety and feasibility in medically complex, high-risk populations is limited. Concerns regarding adverse events frequently hinder treatment initiation and completion in routine clinical practice.

**Objectives:**

The Safety of Preventive Treatment in People at Risk for Tuberculosis (STEP-TB) study aims to generate real-world evidence on the safety of TPT among individuals at high risk of developing active tuberculosis disease and to identify factors associated with adverse events, treatment initiation, adherence, and completion.

**Methods:**

STEP-TB is a multicenter, prospective observational cohort study conducted at four university-affiliated hospitals in the Republic of Korea. Adults aged ≥19 years who are eligible for latent tuberculosis infection (LTBI) testing or TPT according to national guidelines will be enrolled, including individuals with chronic kidney disease, chronic lung disease, diabetes mellitus, immunosuppressive conditions, malignancy, or occupational risk. LTBI testing will be performed using interferon-gamma release assays, and TPT regimens will follow national guidelines. Participants initiating TPT will be followed for up to 12 months from treatment initiation. Those with negative LTBI results or without TPT will be also followed for up to 12 months. Adverse events, treatment adherence, and completion will be systematically assessed. Blood samples, including volumetric absorptive microsampling, will be collected in a subset of participants for pharmacokinetic and pharmacogenetic analyses.

**Outcomes:**

The primary outcome is the occurrence of adverse events during TPT. Secondary outcomes include TPT completion rates, predictors of non-initiation and discontinuation, and progression to active TB.

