**Conclusion:**

STEP-TB will provide condition-specific, real-world evidence on TPT safety and implementation, informing clinical decision-making, patient-centered care, and national TB control policies to support the safe expansion of LTBI treatment strategies in Korea.

**CRIS Registration Number:** KCT0011063

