Building a prospective cohort to collect clinical information on LTBI‑positive individuals is needed to establish a research platform for answering these questions. In this manuscript, we provide an overview of the design, methods and scope of this cohort study. This Safety of Preventive Treatment in People at Risk for Tuberculosis (STEP-TB) study is supported by the Korea National Institute of Health as a national research project. The study findings and datasets will be used as scientific evidence for developing the national TB control master plan in accordance with the TB Prevention Act. We aim to provide evidence to inform national TB policy by evaluating the safety of TPT in the high‑risk groups for active TB disease.

Among the medical high-risk groups for TB, including individuals with chronic kidney disease (CKD), chronic lung disease, diabetes mellitus, malignancy, immunosuppressive conditions, and occupational exposure, the safety of TB preventive treatment remains an important clinical concern. CKD is of special interest because patients with CKD have an increased risk of TB and may be more vulnerable to drug-related adverse events. This study aims to evaluate the safety of TPT in individuals at high risk of developing active TB disease in Korea using a multicenter prospective cohort design. The primary objective is to specifically investigate whether CKD is associated with an increased risk of adverse events during TPT. The secondary objective is to assess the association between CKD and TPT completion, to describe the TPT cascade of care among individuals at high risk of TB, and to evaluate the preventive effectiveness of TPT in reducing progression to active TB during the follow-up period. These objectives will allow a comprehensive understanding of both the safety and effectiveness of TPT in high-risk populations.

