### Statistical analysis

Baseline characteristics of participants undergoing LTBI testing will be summarized using means and standard deviations for normally distributed continuous variables, medians and interquartile ranges for non-normally distributed variables, and frequencies with percentages for categorical variables.

To investigate if the presence of CKD alters the risk of adverse events (present/absent) during TPT, logistic regression models will be built, initially categorizing CKD as a binary variable (present/absent) and then as a ternary variable (present severe, present and not severe, absent). The minimal sufficient adjustment set for inclusion in adjusted models will be derived from a directed acyclic graph (DAG). Potential effect modification by CKD treatment will be explored amongst individuals with CKD. All statistical analyses will be performed using R or SPSS software. Additional analyses will be considered further categorizing the outcome, e.g., on the basis of adverse event severity (ordinal logistic regression) or taking into account the association between an adverse event and the drugs in use. P-values will be corrected for multiple testing.

Assessment of the association between CKD and TPT completion will take place similarly, as will progression to active TB, albeit here using time-to-event models. Finally, the cascade of care analysis will be descriptive.

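### The abstract promises predictors of non-initiation, but the body drops them and fixes the initiation analysis as descriptive

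*Protocol article*

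**What the plan says.** The abstract and the body set different aims.

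- **Abstract, Objectives:** the study is to "identify factors associated with adverse events, treatment initiation, adherence, and completion".
- **Abstract, Outcomes:** "Secondary outcomes include TPT completion rates, predictors of non-initiation and discontinuation, and progression to active TB".
- **Abstract, Conclusion:** "STEP-TB will provide condition-specific, real-world evidence on TPT safety and implementation".
- **Introduction, last paragraph:** "The primary objective is to specifically investigate whether CKD is associated with an increased risk of adverse events during TPT". It continues: "The secondary objective is to assess the association between CKD and TPT completion, to describe the TPT cascade of care", and adds preventive effectiveness. No objective concerns predictors.
- **Outcome measures:** the secondary outcomes are completion, the cascade and effectiveness. Initiation appears only as a proportion within the cascade.
- **Statistical analysis:** adverse events are modelled by logistic regression on CKD, with an adjustment set derived from a directed acyclic graph. Completion is modelled on CKD in the same way, and TB progression gets time-to-event models. On the cascade: "Finally, the cascade of care analysis will be descriptive". Adherence has no analysis of its own.
- **Study population and Table 1:** people may join before testing, after a known result, during TPT, or up to two years after finishing it.

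**The concern.** A protocol article commonly leaves modelling detail to an analysis plan, so silence on predictors would be no finding. Here the document is not silent. It names predictors of non-initiation as a secondary outcome in one place and commits the initiation step to description in another. An analysis plan that added an initiation model would depart from Statistical analysis. One that followed Statistical analysis would leave the abstract's outcome without an adjusted answer.

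Crude initiation proportions by condition mix age with overlapping comorbidities, so they do not show which factors go with non-initiation. As written, nothing restricts those proportions to people whose treatment decision was still open at enrolment. The results are meant to inform national policy on widening TPT, where the reasons treatment is not started are a central question.

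**Working it through.** **1. Aims against analyses**

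| Named in the abstract | Objective in Introduction | Outcome measures | Statistical analysis |
|---|---|---|---|
| Predictors of non-initiation | Cascade to be described | Proportion only | Descriptive |
| Predictors of discontinuation | CKD and adverse events | Partly: the primary outcome is an adverse event that permanently stops a drug | Logistic, CKD as exposure |
| Factors for completion | CKD only | Yes | Logistic, CKD as exposure |
| Factors for adherence | None | Only through the completion definition | None of its own |
| Progression to active TB | Effectiveness | Yes | Time-to-event, exposure not clearly named |

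The first row is the clear contradiction. The next three are narrower than the abstract but partly covered.

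**2. The sizing leaves no non-initiators**

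Inputs from Sample size calculation: 548 initiators, 1,370 enrolled, and 40% used once as the share who test positive and initiate, and once as the positivity rate.

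- Enrolment step: 548 / 0.40 = 1,370, which reproduces the plan's figure.
- LTBI-positive: 1,370 × 0.40 = 548. Initiators: 548. Non-initiators: 548 − 548 = 0.

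Yet Table 2 and the follow-up schedule provide for an untreated LTBI-positive group. (The 548 itself does not reproduce from 20% versus 10% with 15% CKD. The usual pooled two-sided formula gives about 709 to 714, and power at 548 is about 71%. That is a separate matter and does not decide this point.)

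**3. Effect of counting people already treated**

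Let f be the share of LTBI-positive participants enrolled during or after TPT, and r the initiation proportion among the others. The documents give neither. Pooled proportion = f + (1 − f)r, so the excess over r is f(1 − r).

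| Assumed f | Assumed r | Pooled | Excess |
|---|---|---|---|
| 0.10 | 0.90 | 0.10 + 0.90 × 0.90 = 0.91 | 0.01 |
| 0.30 | 0.90 | 0.30 + 0.70 × 0.90 = 0.93 | 0.03 |
| 0.10 | 0.60 | 0.10 + 0.90 × 0.60 = 0.64 | 0.04 |
| 0.30 | 0.60 | 0.30 + 0.70 × 0.60 = 0.72 | 0.12 |

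People enrolled with a known result after treatment had been declined would pull the other way. Restricting to enrolment before the decision removes both effects.

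**4. Whether an initiation model is workable**

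With 548 positives, non-initiators among those enrolled before the decision = 548(1 − f)(1 − r).

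- Low end: 548 × 0.70 × 0.10 ≈ 38.
- High end: 548 × 0.90 × 0.40 ≈ 197.

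The six risk groups named in the abstract plus age and sex make 8 coefficients, so there are 38/8 ≈ 5 to 197/8 ≈ 25 non-initiators per coefficient. This is thin at the low end and comfortable at the high end.

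**5. Precision of by-comorbidity safety estimates**

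Take 548 initiators, borrow the plan's 20% event rate, and assume group shares. Half-width = 1.96 × √(0.20 × 0.80 / n).

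- 5%, n ≈ 27: 1.96 × √(0.16/27) ≈ 15 percentage points.
- 15%, n ≈ 82: 1.96 × √(0.16/82) ≈ 9 points.
- 30%, n ≈ 164: 1.96 × √(0.16/164) ≈ 6 points.

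These are usable as description but too wide for firm ranking of conditions.

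**The case against.** The strongest reply is that the body is consistent with itself. The Introduction sets CKD as the primary question and uses the language of description for the cascade, and Outcome measures and Statistical analysis follow. The outlier is the abstract, and the primary analysis does not depend on it. That stands, and it is why narrowing the abstract is an acceptable repair.

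Several stronger readings are tempting, but the documents do not support them:

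- *The aims cannot be answered.* Comorbidities, medications and social factors are recorded at baseline, and positive participants are classified by TPT receipt. The gap lies in the stated analysis, not in the cohort.
- *Every planned model has CKD as exposure.* This holds for adverse events and completion. For TB progression the exposure is not clearly named, and the Introduction and the analytic framework point to treated versus untreated.
- *Discontinuation is ignored.* Discontinuation because of an adverse event is the primary outcome, though modelled only on CKD.
- *Other conditions' coefficients in the CKD model will be misread.* The plan does not propose to report or interpret them.
- *The reason for not starting TPT is not recorded.* The case report form and the questionnaire are not shown, so this cannot be established.
- *Each condition needs its own causal diagram and model.* A search for predictors or associated factors does not require that.

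**Conclusion.** The point holds as an internal contradiction. One named secondary outcome, predictors of non-initiation, has no planned analysis that answers it, and factors for adherence have none of their own. This rests on the text alone.

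The 1 to 12 point overstatement of the pooled initiation proportion rests on the assumed 10–30% already treated and 60–90% initiation among the rest. It also assumes that the proportion is pooled over all positives, since no restriction is stated.

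The promise of condition-specific evidence is not shown to be empty. CKD is modelled, including by severity, and the Discussion speaks of stratified findings and a cascade across comorbidity groups, which descriptive estimates can supply. A reader might infer that the study should restrict its claims to CKD. That would contradict the body's own cascade and effectiveness aims. The CKD comparison is untouched, and the point should be settled before analysis.

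**What to change.** Choose one of two routes and make the abstract, Introduction, Outcome measures and Statistical analysis agree.

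**Keep the aims.**
1. In Outcome measures and Statistical analysis, add a prespecified secondary, exploratory logistic model of non-initiation. Its population is LTBI-positive participants enrolled before the treatment decision. Its predictors are the named comorbidity groups, age and sex. Report estimates with 95% CIs.
2. Restrict the initiation proportion in the cascade to the same participants.
3. For adverse events and completion, report estimates with 95% CIs by named comorbidity group, labelled exploratory and outside the CKD test.

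**Narrow the aims.** Remove the predictor aims from the abstract's Objectives and Outcomes so that they match the body.

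The cost is protocol wording and a few analyses on data the study already collects. Comorbidities are listed at baseline and age is an eligibility criterion. Sex is not named in the article's condensed list and should be confirmed. The position of enrolment relative to the treatment decision must be derivable from recorded dates. The downside is imprecision in small groups, as shown above. Data collection runs to September 2028 and analysis starts in October 2028, so there is time to amend.

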**Conclusion:**

STEP-TB will provide condition-specific, real-world evidence on TPT safety and implementation, informing clinical decision-making, patient-centered care, and national TB control policies to support the safe expansion of LTBI treatment strategies in Korea.

**CRIS Registration Number:** KCT0011063

## Introduction

Globally, tuberculosis (TB) is the leading cause of death among infectious diseases. Diabetes, human immunodeficiency virus infection, and malnutrition are recognized as major risk factors for developing active TB. According to the World Health Organization (WHO), achieving TB elimination by 2050 requires not only controlling active TB but also implementing treatment for latent TB infection (LTBI) [3]. LTBI is defined as infection with *Mycobacterium tuberculosis* in which a small number of viable bacilli persist in the host without being expelled externally; therefore, there is no transmission to others. Individuals are asymptomatic and have normal acid‑fast bacilli testing and chest radiography. Because residual bacilli cannot be directly detected, LTBI is diagnosed indirectly by measuring the host immune response to TB antigens. Individuals with LTBI are at risk of progressing to active TB disease, and multiple risk factors influence disease progression. Treating LTBI prevents progression to active TB at the individual level and reduces community transmission and overall TB prevalence [4,5].

According to the national TB surveillance data in the Republic of Korea, a total of 19,540 TB cases were notified in 2023, corresponding to an incidence rate of 38.2 per 100,000 population, representing a 9.2% decrease compared with 2022 [1]. Despite this continuous decline, the national TB burden in Korea remains disproportionately high relative to its socioeconomic status [2]. National policies for LTBI management are founded on cost‑effectiveness analyses, for which robust cohort data are essential. Korea has launched the “TB‑Free Korea” program to achieve TB elimination by 2030, with the goal of minimizing progression to active TB among persons with LTBI. To systematically implement LTBI policies, it is urgent to generate scientific evidence on the effectiveness and safety of TB preventive treatment (TPT). Furthermore, the factors associated with progression to active TB among individuals with positive LTBI testing have not been fully defined domestically.

Building a prospective cohort to collect clinical information on LTBI‑positive individuals is needed to establish a research platform for answering these questions. In this manuscript, we provide an overview of the design, methods and scope of this cohort study. This Safety of Preventive Treatment in People at Risk for Tuberculosis (STEP-TB) study is supported by the Korea National Institute of Health as a national research project. The study findings and datasets will be used as scientific evidence for developing the national TB control master plan in accordance with the TB Prevention Act. We aim to provide evidence to inform national TB policy by evaluating the safety of TPT in the high‑risk groups for active TB disease.

Among the medical high-risk groups for TB, including individuals with chronic kidney disease (CKD), chronic lung disease, diabetes mellitus, malignancy, immunosuppressive conditions, and occupational exposure, the safety of TB preventive treatment remains an important clinical concern. CKD is of special interest because patients with CKD have an increased risk of TB and may be more vulnerable to drug-related adverse events. This study aims to evaluate the safety of TPT in individuals at high risk of developing active TB disease in Korea using a multicenter prospective cohort design. The primary objective is to specifically investigate whether CKD is associated with an increased risk of adverse events during TPT. The secondary objective is to assess the association between CKD and TPT completion, to describe the TPT cascade of care among individuals at high risk of TB, and to evaluate the preventive effectiveness of TPT in reducing progression to active TB during the follow-up period. These objectives will allow a comprehensive understanding of both the safety and effectiveness of TPT in high-risk populations.

## Materials and methods

### Study design, and setting

The STEP-TB is a multi-center prospective observational cohort study conducted at four university-affiliated hospitals participating in the national Public-Private Mix Tuberculosis Control Project [3] in the Republic of Korea. The participating institutions include Seoul St. Mary’s Hospital, Incheon St. Mary’s Hospital, Yeouido St. Mary’s Hospital, and Daejeon St. Mary’s Hospital, all of which are tertiary-care centers affiliated with the Catholic University of Korea. Additional research sites may be added after protocol publication to expand recruitment capacity. Participant enrollment is scheduled to begin in October 2025 and will continue through December 31, 2027. Recruitment is expected to be completed by August 2027. Data collection is anticipated to conclude by September 2028. Data analysis is planned for October through December 2028, and the reporting of study results is expected to be completed in January 2029.

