VAMS sampling			O	O		
Questionnaire		O				

V, visit; D, day; W, Week; M, Month; EOT, End of Treatment; EOS, End of Study; TB, tuberculosis; VAMS, volumetric absorptive microsampling.

To assess the development of incident active TB, an additional follow-up visit will be conducted 12 months after TPT initiation (end of study).

To evaluate drug pharmacokinetics and pharmacogenetic profiles, blood samples will be collected using Volumetric Absorptive Microsampling (VAMS). VAMS collection will be performed at the planned visits (Week 2 and Week 4), precisely 3 hours (±5 minutes) after the participant takes the anti-TB medication. Participants will be instructed to take the medication at a consistent time in the morning before breakfast, and the exact time and date of drug administration and sampling will be recorded in the case report form.

For participants with negative LTBI results, or for those who test positive but do not receive TPT, follow-up assessments will be conducted at 6 months and 12 months after baseline, after which the study will conclude (Table 4). The occurrence of active TB will be evaluated throughout the follow-up period.

**Table 4 pone.0350186.t004:** Study visit schedule and assessments for participants with negative latent tuberculosis infection results or without tuberculosis preventive treatment.

Visit	V0	V1	V3	V4
Visit name	Screening	Baseline	6 months	EOS
Timing	−D14	D0	M3–10	M11–15
Informed consent	O			
Medical history	O	O	O	O
Chest imaging		O	O	O
Questionnaire		O		

V, visit; D, day; W, Week; M, Month; EOT, End of Treatment; EOS, End of Study

Study participation may be discontinued under specific circumstances. Participants who withdraw their informed consent will discontinue further study procedures. Investigator may also discontinue participant’s involvement if, in their clinical judgment, continued participation is deemed inappropriate due to medical, safety, or other relevant considerations. Participants who discontinue study participation will not be excluded from the analysis. Instead, all available data up to the point of discontinuation will be retained and reported where applicable.

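### Two closing dates are given for enrolment, and only August 2027 lets the 12-month visit take place before data collection ends in September 2028

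*Protocol article*

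**What the plan says.** The calendar is in the protocol article under Study design, and setting. On enrolment it says: "Participant enrollment is scheduled to begin in October 2025 and will continue through December 31, 2027". The sentence that follows reads: "Recruitment is expected to be completed by August 2027". Then: "Data collection is anticipated to conclude by September 2028". After that, "Data analysis is planned for October through December 2028", and reporting is to be finished in January 2029.

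The length of follow-up is set under Study procedures. For treated participants: "To assess the development of incident active TB, an additional follow-up visit will be conducted 12 months after TPT initiation". For test-negative participants, and for test-positive participants who do not receive TPT, "follow-up assessments will be conducted at 6 months and 12 months after baseline, after which the study will conclude". Tables 3 and 4 give the end-of-study visit a window of months 11 to 15. The abstract words the treated follow-up a little more loosely: "Participants initiating TPT will be followed for up to 12 months from treatment initiation".

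**The concern.** The article draws no distinction between enrolment and recruitment, so two closing dates four months apart stand next to each other. The later one cannot be combined with a 12-month visit and a September 2028 end of data collection.

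A site that works to the December date would enrol people whose final assessment for active TB falls after data collection has closed, and for the latest of them after the planned analysis period as well. That visit is the last scheduled look for incident active TB, which the secondary objective on preventive effectiveness relies on. For a 9H course started late, the 12-month period in which completion is judged (Treatment adherence and completion) would also still be open at the close.

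**Working it through.** **Inputs, all from the protocol article**

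- Enrolment start: October 2025, taken as 1 October 2025 (Study design, and setting).
- Closing dates: August 2027, taken as 31 August 2027, and 31 December 2027 (same section).
- End of data collection: September 2028, taken as 30 September 2028, the most lenient reading (same section).
- End-of-study visit: month 12, window months 11 to 15 (Study procedures; Tables 3 and 4). Day 0 is TPT initiation for treated participants and baseline for the others.
- Target enrolment: 1,370 (Sample size calculation).

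**Step 1. Does September 2028 follow from either closing date?** Last visit = last day 0 + 12 months.

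- 31 August 2027 + 12 months = 31 August 2028. This is before 30 September 2028, so the plan's own date is reproduced, with about 30 days to spare.
- 31 December 2027 + 12 months = 31 December 2028. This is 92 days after the close. The earliest in-window visit, month 11, is 30 November 2028, which is 61 days after it. Such a participant has nine months of follow-up when data collection ends.

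**Step 2. Latest day 0 that still works.** Latest day 0 = 30 September 2028 − visit month.

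- Month 12: 30 September 2027.
- Month 11, the earliest in-window visit: about 30 October 2027.

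**Step 3. How many could be affected.** Assume even accrual over the 27 months from October 2025 to December 2027 and day 0 at enrolment. Neither is stated in the article.

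- Enrolled October to December 2027, month 12 out of reach: 1,370 × 3/27 ≈ 152 (11%).
- Enrolled November to December 2027, no in-window visit: 1,370 × 2/27 ≈ 101 (7%).
- Counting days gives nearly the same: 92/822 = 11.2%, or about 153, and 61/822 = 7.4%, or about 102.
- If the target is filled by August 2027, as the second sentence expects, and day 0 follows by 30 September 2027: 0.

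**Step 4. Which outcomes are touched.** Take the latest case, TPT started on 31 December 2027.

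| Regimen | Nominal end | Completion window closes |
|---|---|---|
| 3HR | 31 March 2028 | 30 April 2028 (4 months) |
| 4R | 30 April 2028 | 30 June 2028 (6 months) |
| 9H | about 30 September 2028 | 31 December 2028 (12 months) |

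The primary outcome is an adverse event during TPT that leads to permanent discontinuation of a drug (Outcome measures), and Table 3 schedules no adverse event assessment at the end-of-study visit. Treatment-period data for 3HR and 4R are therefore in hand months before the close. A 9H course taken on schedule ends at about the close itself. What remains exposed is a delayed 9H course, the 12-month 9H completion window, and TPT started well after a late enrolment.

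**The case against.** The strongest reply is that the calendar works on one of its own stated dates. With August 2027 the sequence of visits, data collection, analysis and reporting is in order, and December could be meant as an outer limit with August as the expected finish. That is fair as far as it goes, and it means the loss of visits is conditional on enrolment actually running late. But the sentence presents December as the date to which enrolment continues, and nothing marks it as a contingency. Nor does the abstract's looser wording on length of follow-up remove the conflict, because Study procedures schedules the visit at 12 months.

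Three stronger readings are tempting, and the document does not support them.

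- *That the primary safety comparison is compromised.* The visit at risk serves incident active TB, which is secondary and is to be analysed with time-to-event models. Those can use follow-up cut off by the calendar, so the likely cost is precision. No bias has been shown.
- *That treated participants lose more.* It is true that the treated clock starts at TPT initiation, which for a new starter comes after enrolment. But Study population also admits people already on TPT, or who completed it within the past two years, and their 12 months began before they enrolled. The net direction depends on a mix that the article does not give.
- *That August 2027 fails too, because month 15 would be 30 November 2028.* The visit is scheduled at 12 months, and months 11 to 15 are a tolerance around it. A plan need not hold the whole tolerance open for its last participant.

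**Conclusion.** The inconsistency is real and the date arithmetic is not in doubt: 31 December 2027 cannot stand beside a 12-month visit and a September 2028 close, while August 2027 can. It should be corrected, but it is a modest point.

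Its size ranges from no visits lost, if recruitment closes in August 2027 and day 0 follows within about 30 days, to at most about 152 of 1,370 (11%) without a month-12 visit and about 101 (7%) without any in-window visit, if accrual is even up to 31 December 2027. These are upper bounds in that they give every late enrolee a clock starting at enrolment, whereas people enrolled on or after TPT count from an earlier date. They do take day 0 as no later than enrolment. A gap between consent and TPT start would work the other way, and Table 3 gives no limit from which to size it.

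The effect falls on incident active TB and on the completion window of late-started 9H. The primary outcome is largely unaffected.

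**What to change.** State one closing date and set the rest of the calendar from it. Either route works:

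- **Keep August 2027 and September 2028.** Delete the 31 December 2027 date. Add that a month-12 visit before the close requires day 0 (baseline or TPT start) no later than about 30 September 2027. This is a limit on the study calendar for planning enrolment, not a rule about when treatment is given.
- **Keep 31 December 2027.** Delete the August date and move the end of data collection to at least 12 months after the last day 0, so the end of December 2028 or later. A three-month shift would put analysis at about January to March 2029 and reporting at about April 2029, and later still if TPT can start some time after enrolment.

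The first route costs a change of wording. The second costs a delay of a few months in database lock and reporting.
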